#### Data collection

Quantitative data on numbers of patients, HCPs and long COVID-19 clinics registered to use LWCR. Additionally, patient demographic data, clinical and service data and app usage patterns, as recorded through the LWCR platform will be provided.

Demographic data will be obtained on patients’ age, gender, ethnicity, highest level of educational attainment and socioeconomic status (using Index of Multiple Deprivation, calculated from the postcode) when patients first register on the app. This data will be entered by HCPs or the patients themselves.

Clinical data will be obtained from patient-completed PROMs on the app. Patients will be asked to complete all the PROMs at baseline to help with clinical assessment, and thereafter, only those PROMs which the clinician and patient deem to be clinically relevant and helpful for clinical management.

Validated PROMs include: the Work and Social Adjustment Scale which measures functional impairment and is our primary outcome measure^26^; EuroQol 5 dimensions, 5 response level instrument (EQ-5D-5L) for health related quality of life^27^; Functional Assessment of Chronic Illness Therapy - Fatigue (FACIT-F) for fatigue^28^; Generalised Anxiety Disorder Assessment (GAD-7) for anxiety^29^; Personal Health Questionnaire Depression Scale (PHQ-8) for depression^30^; Medical Research Council (MRC) dyspnoea scale^22^ and Dyspnoea-12^31^ for breathlessness, and Perceived Deficits Questionnaire-5 item (PDQ-5) for cognitive impairment.^32^ Additional questions explore levels of physical activity and overall recovery from COVID-19.

Service use data will be obtained when patients complete a service use questionnaire (every 4 weeks), detailing the number of healthcare appointments, days off work and days as a hospital inpatient they have experienced.

Usage data including the date and time of each page view by each patient are recorded automatically by the programme.

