#### Participants

The target for year 1 will be to recruit 1000 patients registering with the DHI. This will enable us to estimate the overall proportion of patients engaging with the app with a high-level of precision (maximum width of 95% CI is ±3.2%). Similar or increased levels of precision will be achieved when estimating the proportion of those referred who register with the intervention. The sample size in year 2 has not been prespecified and will depend on practical constraints imposed by the scale of the pandemic as the digital intervention is rolled out nationally. Power calculations will be carried out for the year 2 analyses based on the ‘pilot’ data from year 1. This will include power for the proposed quasi-experimental analysis of the effect of the DHI on outcomes at 3-month and 6-month follow-up.

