##### Missing data

Sensitivity analyses will be conducted to examine the influence of missing data on the key study findings. This will include the use of multiple imputation methods, where the assumption that the data are missing at random is considered appropriate, and tipping point analysis^34^ to assess sensitivity of the results to data that are missing not at random.

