## Discussion

This protocol describes the processes for developing, deploying and evaluating digitally enabled remote, supported rehabilitation for people with long COVID-19 syndrome. Strengths include the inter-disciplinary approach, with a partnership between patients, clinicians, industry and academics, plus combining approaches used in engineering/computer science, for example, UCD and the HCI lifecycle, with those more familiar to biomedical researchers, for example, the MRC Framework for complex interventions. The strong use of theory to underpin the research should enhance transferability of findings. Putting equal priority on service needs and research is innovative, but brings challenges. These include relying on diversity of service delivery for obtaining an appropriate comparator and the reliance on data obtained for clinical purposes for the impact evaluation. We expect there to be substantial amounts of missing data, particularly in the PROMs, as clinicians and patients are likely to focus on recording symptoms of most interest to them or suffer from questionnaire fatigue. However, no one study can answer all relevant research questions about an innovation, and we agree with the argument that a DHI should achieve a reasonable level of stability before being evaluated in a randomised controlled trial.^38^ This initial study will provide considerable insight into patient, clinician and health service requirements for digitally supported rehabilitation for long COVID-19, together with very substantial, real world data on acceptability, uptake and use, going far beyond the usual pilot studies so often used as evidence of acceptability and feasibility, with data on scalable, and hopefully, sustainable, deployment. It will also generate data on symptoms and illness trajectories in a treatment-seeking population which includes non-hospitalised patients, making it unique among current cohort studies. Long-term investment will require causal evidence of effectiveness, and NIHR has funded the STIMULATE-ICP project, which includes a cluster randomised controlled trial comparing LWCR to standard care,^39^ due to report in 2023. Other future work will consider whether a digital tool could help stratify long COVID-19 patients by their clinical severity^40^ or combine with other digital help products such as telemedicine to achieve better outcomes.^41^

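### After baseline the primary outcome (WSAS) is requested only when clinician and patient judge it relevant, so its 3- and 6-month values are selectively collected by design and plausibly informative

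*Protocol article*

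**What the plan says.** WP3 Data collection sets two rules for PROMs. At entry, "Patients will be asked to complete all the PROMs at baseline to help with clinical assessment"; "thereafter, only those PROMs which the clinician and patient deem to be clinically relevant and helpful for clinical management". The next paragraph lists the PROMs, beginning with "the Work and Social Adjustment Scale which measures functional impairment and is our primary outcome measure". Nothing exempts WSAS from the discretionary rule, and no WSAS assessment is fixed at 3 or 6 months. The service use questionnaire in the same section does have a fixed interval of 4 weeks.

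WP3 Participants says that year 2 power calculations will include "power for the proposed quasi-experimental analysis of the effect of the DHI on outcomes at 3-month and 6-month follow-up".

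The Discussion expects substantial missing PROM data because "clinicians and patients are likely to focus on recording symptoms of most interest to them", or because of questionnaire fatigue. The Missing data section plans "multiple imputation methods, where the assumption that the data are missing at random is considered appropriate" and a tipping point analysis for data missing not at random, both as sensitivity analyses.

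**The concern.** The collection rule and the intended use of WSAS do not fit together. Whether a functional-impairment scale still seems worth completing plausibly depends on how well the patient is functioning at that moment, and that value is exactly what goes unrecorded if the scale is not requested. If so, the observed WSAS scores come from a selected subset, and the selection is related to the outcome itself.

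Several WP3 analyses would be affected:

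- **Recovery trajectories.** Mixed models and latent class models use the observed scores and assume MAR.
- **Population impact.** WP3 defines this as reach times effect. Reach covers the whole eligible or registered group, while effect would come only from those still being monitored on WSAS.
- **Mediation analysis.** The number of assessments completed is an explanatory factor, so exposure and the chance of observing the outcome are linked.
- **Equality interactions.** These are distorted if selection differs between groups.
- **Any comparison with external cohorts.** Propensity methods for measured confounders do not correct for selective outcome collection in one arm.

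A larger number of registrants does not reduce this kind of bias. Once a follow-up time has passed, the scores cannot be obtained.

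**Working it through.** **1. The plan's own figure.** The only sample-size figure is a maximum 95% CI half-width of ±3.2% for the proportion engaging, with n = 1000. At p = 0.5, 1.96 × sqrt(0.25/1000) = 3.10%; the exact interval gives 3.15%; with z taken as 2, 1/sqrt(1000) = 3.16%, which rounds to 3.2%. The figure reproduces. It concerns engagement, not WSAS, and this point leaves it untouched.

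**2. The text.** WSAS is a PROM (WP3 Data collection). Every PROM after baseline is discretionary (same section). WSAS is the primary outcome (same section). Outcomes at 3 and 6 months are analysed (WP3 Participants). Hence the 3- and 6-month primary outcome exists only where someone chose to monitor it. This step needs no assumption.

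**3. What selection can do to a MAR analysis.** The document gives no WSAS SD, expected change or completion rate, so every input here is assumed.

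- Baseline WSAS: mean 22, SD 9.
- Follow-up = baseline + N(-3, 7), clipped to 0-40; the realised true mean change is -2.89.
- logit P(completed) = a + [ln(OR)/10] × current WSAS, with a set to give the stated completion.
- Estimate: change regressed on baseline among completers, then standardised to all patients, which is a simple MAR analysis. Relative bias = |estimate - (-2.89)| / 2.89.

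| Completion | OR per 10 points | Estimate | Relative bias |
|---|---|---|---|
| 32% | 0.5 | -4.96 | 2.07/2.89 = 72% |
| 32% | 2 | -0.89 | 2.00/2.89 = 69% |
| 50% | 0.5 | -4.42 | 1.53/2.89 = 53% |
| 50% | 0.8 | -3.36 | 0.47/2.89 = 16% |
| 50% | 1 | about -2.89 | about 0 |
| 50% | 1.25 | -2.41 | 0.48/2.89 = 17% |
| 50% | 2 | -1.44 | 1.45/2.89 = 50% |
| 70% | 0.5 | -3.8 | 0.91/2.89 = 31% |
| 70% | 2 | -2.0 | 0.89/2.89 = 31% |

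A rerun with a different random seed gave the same values to within simulation error.

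**4. A second parameterisation.** Take a standardised follow-up score, baseline correlation 0.3-0.7, completion 30-70% and log-odds of completion 0.25-1.0 per SD of the current score. Residual bias after baseline adjustment is about 0.04 to 0.55 SD. With 50% completion, correlation 0.5 and log-odds 0.5, completers alone are off by about 0.24 SD, and about 0.18 SD remains after adjustment.

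**5. The benign case.** If completion depends only on the recorded baseline score (log-odds 0.5 per SD), residual bias after adjustment is about 0. The conclusion therefore turns on whether the choice of PROMs uses information that the platform does not record.

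**The case against.** Five points can be made for the plan, and most of them stand in part.

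**The mechanism is not proven.** A reader might infer that the data are MNAR as a matter of design. The document does not establish that. The rule refers to clinical relevance and says nothing of unrecorded current function. Because all PROMs are requested at baseline, the choice may follow recorded scores, and then MAR could hold. WSAS also measures general function, so dropping a PROM because its symptom is of little interest applies to it less clearly than to a breathlessness or anxiety scale. Observed data cannot settle the matter. What the text does establish is selective collection; that it is informative is a plausible inference.

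**The Discussion is less specific than it may seem.** It speaks of symptoms of interest and of questionnaire fatigue. It does not say that recovered patients stop or that very unwell patients drop out.

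**MNAR is not ignored.** Imputation is restricted to where MAR is thought appropriate, and a tipping point analysis is planned. That is to the plan's credit, but it shows how far conclusions could move and does not fill in unrequested scores.

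**The simulation is harsher than the planned analysis.** Mixed models would use interim scores, and the service use, activity and recovery items could serve as auxiliaries. With an assumed auxiliary correlated 0.76 with the current score and 50% completion, the range -4.4 to -1.4 narrows to -3.9 to -1.9. Its width falls from 3.0 to 2.0, so about a third of the bias goes and the rest remains.

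**The study is service-embedded and exploratory.** There is no comparator arm, a synthetic comparator is only a feasibility question, and causal evidence is left to a separate cluster randomised trial. This limits what depends on WSAS. It does not explain why the one measure named as primary should be optional.

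**Conclusion.** The point holds in this form: the protocol makes follow-up collection of its primary outcome discretionary, with no exemption, while planning to analyse outcomes at 3 and 6 months. Collection is selective by design and plausibly informative. The planned MAR methods may not correct it, and the tipping point analysis cannot recover it.

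The size and sign of the bias are unknown. The range of about -5.0 to -0.9 around a true change of -2.9 rests wholly on assumed inputs. Its ends belong to strong selection (a factor of 0.5 or 2 per 10 points) at low completion. A reader might take a bias of half the true change or more as typical. The calculation does not support that: the bias is about 16% at 0.8 or 1.25 with 50% completion and vanishes at a factor of 1. The numbers show that a material bias is possible, not that it is expected.

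**What to change.** For follow-up still to come:

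1. Exempt WSAS from the discretionary rule. Request it from every registered patient alongside the 4-weekly service use questionnaire, whichever other PROMs are chosen. The third and sixth cycles fall at 12 and 24 weeks.
2. Define analysis windows around 3 and 6 months, and use the scheduled WSAS for the primary outcome analyses.
3. Leave the other PROMs discretionary, and describe their trajectories as conditional on being monitored.
4. Record why a WSAS score is missing, where this can be known.
5. Keep the planned MNAR sensitivity analysis.

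The cost is an app scheduling change, a sentence or so in WP3 Data collection, and a slightly longer 4-weekly prompt with some added questionnaire burden. WP1 Outputs already foresees updates to questionnaires every few months, so the change fits the planned releases. The service use questionnaire is itself voluntary, so the change removes selective requesting but not non-response.

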#### Data analysis

Each patient will be assigned a unique participant identification number. The linking key will be held by Living With, as data processors for the Clinical Trusts. Pseudonymised data, where date of birth is replaced by age and postcode replaced with IMD, will be shared with the research team. Demographic characteristics and baseline symptoms of the registered ‘treatment seeking’ population of long COVID-19 sufferers will be profiled using descriptive statistics.

##### Usage and engagement

Patient engagement with the app will be reported using a stratification of patients into low, medium and high categories based on number of logins over the first 12 weeks. Demographic and baseline clinical factors influencing uptake and use will be identified through logistic regression, with multivariate methods used to model patterns of app engagement over time.

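### Counting logins does not separate questionnaire visits from use of rehabilitation content, which matters most in the mediation and dose–response models

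*Protocol article*

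**What the plan says.** All places are in the protocol article.

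- **WP3, Usage and engagement.** Engagement is reported by sorting patients into "low, medium and high categories based on number of logins over the first 12 weeks". Logins are not separated by purpose. Demographic and baseline clinical predictors of uptake and use are then sought by logistic regression.
- **WP3, Data collection.** "Clinical data will be obtained from patient-completed PROMs on the app". At the start, "Patients will be asked to complete all the PROMs at baseline to help with clinical assessment"; after that, "only those PROMs which the clinician and patient deem to be clinically relevant and helpful for clinical management". A service use questionnaire follows every 4 weeks, and service data are among the items recorded through the platform. The same section states: "Usage data including the date and time of each page view by each patient are recorded automatically by the programme".
- **WP3, Mediation analysis of intervention components.** Intervention components and two patient-usage measures, logins and completed assessments, enter the longitudinal outcome models. A dose–response relation between app usage (or new content) and outcome change is then examined.
- **Strengths and limitations.** There is no comparator group. The mediation analysis is called exploratory, but it is one of the two stated focuses of the evaluation.
- **Abstract; Aims and objectives.** Assessment and monitoring are part of the digital intervention, and the rehabilitation is tailored to symptoms.

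**The concern.** A login can mean that the patient came to use rehabilitation content, to answer a questionnaire, or both. For describing how much the app is used, that mixture is tolerable. For a dose–response analysis it is not, because the dose of interest is use of the rehabilitation.

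The outcome is a PROM completed in the app, so it can be observed only when the patient is in the app. Part of the login count is thus the act of measuring the outcome. If the models show that more logins go with better or worse change, the reader cannot tell whether this reflects treatment use or the pattern of assessment. Without a comparator, these models carry much of the interpretation of what the programme does.

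A second route is possible. Follow-up PROMs are chosen by clinician and patient for relevance. If patients with more symptoms are assessed on more occasions, their login counts rise without any extra use of content.

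**Working it through.** **The plan's own figure.** The only number attached to engagement is the year 1 precision of ±3.2% for n = 1000 (WP3, Participants). At p = 0.5:

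- Normal approximation: 1.96 × √(0.25/1000) = 3.10%.
- With continuity correction: 3.10% + 1/(2 × 1000) = 3.15%. The exact interval also gives 3.15%.

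The stated value is reproduced if rounded up. It describes sampling error only and says nothing about what a login represents.

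**Step 1: scheduled questionnaire occasions in the 12-week window.** Service questionnaires: 12/4 = 3 (weeks 4, 8, 12). Baseline PROM session: 1. Total q = 3 + 1 = 4, with no rehabilitation page opened. This assumes one login per occasion and completion in the app. The article places PROMs on the app explicitly, but says only that service data are recorded through the platform.

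**Step 2: share of all logins.** With r content logins, share = q/(q + r). The values of r, and the 6 follow-up PROM logins in the second row, are assumptions.

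| Content logins r | 2 | 5 | 10 | 20 | 40 |
|---|---|---|---|---|---|
| q = 4 (no follow-up PROM logins) | 67% | 44% | 29% | 17% | 9% |
| q = 10 (6 follow-up PROM logins) | 83% | 67% | 50% | 33% | 20% |

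For example, 4/(4 + 2) = 67% and 10/(10 + 40) = 20%. The mixture could be large among light users and small among heavy users.

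**Step 3: does it distort comparisons between patients?** The 4-weekly schedule is the same for everyone. Adding the same number to every count changes no ranking, so a division into thirds would be unchanged. Distortion needs questionnaire or PROM sessions that differ between patients.

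An illustrative simulation shows the dependence. It used 400,000 patients; content logins negative binomial (k = 1) and independent of severity; four-weekly questionnaires each completed with probability 0.7; Poisson PROM sessions; and the high group defined as the top third of total logins. The odds ratio for being in the high group, more versus less symptomatic, has a true value of 1.0:

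| Mean PROM sessions, more vs less symptomatic | Mean content logins 4 | 8 | 16 |
|---|---|---|---|
| equal | 0.99–1.00 | 0.99–1.00 | 0.99–1.00 |
| 2 vs 1.5 | 1.19 | 1.09 | 1.04 |
| 3 vs 1 | 1.99 | 1.45 | 1.22 |
| 6 vs 1 | 5.22 | 2.48 | 1.58 |

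The whole effect comes from the assumed difference in PROM sessions, which the article does not give.

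**Step 4: the link in the outcome models.** Write total logins as L = C + A + B, where C is content-only, A is questionnaire-only and B is both. Follow-up outcomes arise only in A and B. Unless the app stays open between visits, a patient with no login after baseline has no observed change. Exposure and outcome observation therefore share the terms A and B whatever the login rates. Entering completed assessments beside logins separates them only in part: several assessments can be done in one login, and a B session adds to both counts.

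**The case against.** The strongest case against has four parts.

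1. **Questionnaires belong to this intervention.** It is built to support assessment and monitoring, and PROM data inform the tailoring. A questionnaire login is real use of the app, and the section measures engagement with the app. This stands, and is why total logins should remain the descriptive measure.
2. **Nothing is compulsory, and frequency is not set.** A reader might infer that the protocol requires these logins, or that sicker patients collect more of them by design. The text says patients are asked, governs which PROMs are completed and not how often, and the Discussion expects many PROMs to be missing. Several PROMs can share a login, and a questionnaire can be answered during a content visit. This stands: an effect of symptom burden is possible, not shown.
3. **Wider consequences do not follow.** A reader might infer that the year 1 proportion engaging, and hence reach, is overstated, or that predictors of use are biased. The aim to "estimate the overall proportion of patients engaging with the app with a high-level of precision" is not tied to the login categories, and the logistic regression is not said to use them as its outcome. This stands.
4. **The mediation section has more than logins.** It also names intervention components, assessments completed and new content, and is exploratory. This stands in part. How components are measured is not stated, and if page views are used, some of the remedy is already there. But the patient-usage measures it names are logins and assessments completed, and neither is use of rehabilitation content.

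**Conclusion.** The point holds in limited form. Logins mix data collection with use of rehabilitation content. In the mediation and dose–response models this ties the exposure partly to outcome measurement, so a gradient on logins cannot be read as a gradient on rehabilitation. That conclusion rests on the text alone: PROMs are completed on the app, and logins are an explanatory factor for PROM change.

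The size cannot be established. The count of about 4 scheduled occasions assumes one in-app login each. The shares (9% to 83% over the assumed range) and the odds ratios (about 1.0 to 5.2) depend on login rates and PROM frequencies that the article does not give. They show what could happen, not what will. The documents do not support a claim that engagement or reach is in fact overstated, or that more symptomatic patients will in fact appear more engaged. This is a cheap improvement, not an error that invalidates the analysis.

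**What to change.** **Mediation and dose–response models.** From the existing time-stamped page-view log, derive the number of days after registration on which at least one rehabilitation content page was opened. Make this the main patient-usage exposure. Keep logins and assessments completed as separate measures.

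**Usage and engagement.** Keep total logins as the measure of engagement with the app. Report questionnaire-only sessions separately, and repeat the analysis of predictors of use with the content-page measure.

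**Cost.** No new data are collected. App pages must be classified as content or assessment, and the classification kept current, because WP1 Outputs foresees updates every few months. Reported use will be lower. The measure does not remove all dependence on symptoms: content is tailored to them, so content use may vary with symptom burden too. It removes the direct overlap with outcome measurement, not confounding.

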### Aims and objectives

The aim is to iteratively design, deploy and evaluate a digitally mediated, remote, supported rehabilitation programme for patients affected by COVID-19, which is used effectively, deployed at scale, and does not widen health inequalities.

Specific objectives are to:

Develop and refine a DHI that supports patient monitoring, remote rehabilitation and identifying patients needing further specialist investigation. To include:Clinical pathways aligned with National Institute for Health and Care Excellence guidelines.^20^A clinician-facing digital dashboard which displays data about individuals and selected cohorts.A patient-facing mobile app to provide targeted, tailored rehabilitation according to patient symptoms. The app will collect patient-reported outcome measures (PROMs) and use intelligent algorithms and machine learning to promote engagement and tailor treatment advice under clinician guidance.Determine implementation strategies to promote adoption, scale-up, spread and sustainability with a view to maximising population impact. To include assessing:How best to integrate the DHI into clinical workflows, so it becomes fully normalised for healthcare professionals (HCPs), and patients experience seamless care.The optimal amount of HCP input (time, skill set) required to support patients to engage effectively with the DHI, including those with low digital literacy, while managing large patient workloads safely.Funding and commissioning models to promote long-term sustainability.Assess the population impact of this model of care. To include:Determining the reach (uptake and engagement) of the DHI, as a proportion of eligible patients and how this varies by demographic characteristics.Exploring its impact on patient-reported outcomes and recovery trajectories.Assessing the cost implications to the National Health Service (NHS) of scaling-up and sustaining it.Determine and mitigate the effect of the digital divide on health inequalities.Identify patterns of differential uptake, use and apparent benefits of the DHI for people from ethnic minority or socially disadvantaged backgrounds.Identify and test actions to mitigate any observed differential.

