#### Data collection

We will use qualitative methods in real-time, including online meetings, interviews and focus groups with the three stakeholder groups, recorded with participant consent. Meetings will be driven by both research and service need to provide real-time insight into the needs of patients, health service managers and HCPs, as they adapt to the evolving pandemic, without imposing additional workload. Documents, including meeting agendas and minutes, and follow-up emails, will also be used as data sources.

Quantitative data: see WP3. For ethical reasons we are unable to contact or collect data directly from patients who have declined the LWCR service.

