##### Equality

The acceptability of the intervention for people from disadvantaged backgrounds will be explored through logistic regression analysis of these factors as predictors of recruitment, usage and retention. Differential effects of the DHI on outcomes for disadvantaged groups will be investigated through inclusion of interactions between intervention uptake and ethnicity, age, educational status and IMD in the GLMMs.

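### Predictors of registration cannot be estimated from the data described: every patient-level covariate is captured at or after registration

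*Protocol article*

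**What the plan says.** Two analyses in WP3 need people who did not take up the digital health intervention (DHI).

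- Usage and engagement: "Demographic and baseline clinical factors influencing uptake and use will be identified through logistic regression".
- Equality: acceptability for disadvantaged groups is to be examined through "logistic regression analysis of these factors as predictors of recruitment, usage and retention".

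They serve two stated objectives (Aims and objectives): "Determining the reach (uptake and engagement) of the DHI, as a proportion of eligible patients and how this varies by demographic characteristics", and "Identify patterns of differential uptake, use and apparent benefits of the DHI for people from ethnic minority or socially disadvantaged backgrounds".

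The data for them are described as follows.

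- WP3, Data collection: demographics are obtained "when patients first register on the app", and "This data will be entered by HCPs or the patients themselves". Clinical data come from patient-reported outcome measures (PROMs) completed in the app. The counts listed are of registered patients, professionals and clinics.
- WP1, Data collection, which refers the reader to WP3 for quantitative data: "For ethical reasons we are unable to contact or collect data directly from patients who have declined the LWCR service".
- WP2, Data collection: the one count of non-adopters is of Trusts, not patients.
- WP3, Participants: the year 1 target is 1000 registrants, and the plan also expects to estimate the "proportion of those referred who register with the intervention".

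**The concern.** A logistic model of registration compares people who registered with people who did not, on covariates known for both. In the data described, a patient acquires covariates only by registering, so everyone who could enter the model has the same outcome. The analysis stated and the data stated do not fit together.

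What is at stake is the demographic breakdown of reach (part of objective 3) and differential uptake (part of objective 4). Followed as written, the model either fails to fit or turns into a model of use among people who have already registered. The second outcome is the more harmful, because those excluded at the point of registration are no longer in the data. An analysis of registrants could then be reported as evidence on equity of uptake.

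**Working it through.** **The plan's own figure.** For n = 1000 registrants the largest 95% half-width is z × √(0.5 × 0.5 / 1000). With z = 1.96 this is 3.10%, and with z rounded to 2 it is 3.16%, which rounds to the stated ±3.2%. The point below does not depend on this figure.

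**Step 1: fit the registration model to the patients who have covariates.** All 1000 outcomes equal 1. With the slope at zero and intercept k, the log-likelihood is −1000 × ln(1 + e^(−k)):

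- k = 5: −6.7
- k = 10: −0.045
- k = 20: about 0

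It keeps rising, so no finite maximum exists. A trial fit with one binary covariate (200 against 800 patients) reported perfect separation and standard errors above 10,000. No uptake effect is estimable.

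**Step 2: add a total count of referred patients.** The sample-size text implies such a count but gives no number. The uptake values below are assumptions. Referred = 1000/u, and half-width = 1.96 × √(u(1−u)/referred).

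| Assumed uptake u | Referred | Not registered | 95% half-width |
|---|---|---|---|
| 50% | 2000 | 1000 | ±2.2% |
| 70% | 1429 | 429 | ±2.4% |
| 90% | 1111 | 111 | ±1.8% |

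Overall uptake can therefore be estimated from counts alone, and with better precision than ±3.2%, in line with what the plan expects.

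**Step 3: ask for a demographic effect with that count only.** Assume 200 of the 1000 registrants (20%) are in a disadvantaged group, and let s be that group's share among non-registrants. The odds ratio for uptake is (200/800) ÷ (s/(1−s)) = 0.25 × (1−s)/s. It does not depend on u. The last two columns take u = 70%.

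| Assumed s | Odds ratio | Uptake, disadvantaged group | Uptake, others |
|---|---|---|---|
| 10% | 2.25 | 82.3% | 67.4% |
| 20% | 1.00 | 70.0% | 70.0% |
| 30% | 0.58 | 60.8% | 72.7% |
| 40% | 0.375 | 53.8% | 75.7% |

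The article describes no source that would supply s, so even the direction of any inequality in uptake is undetermined.

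**Step 4: baseline clinical factors.** These come from PROMs completed in the app. A patient who never registers never completes one, so they cannot be predictors of registration whatever referral data are obtained.

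**The case against.** Five arguments can be made for the plan.

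1. *Non-events do exist.* A reader might infer that nothing at all is known about people who do not register and that reach cannot be estimated. The documents do not support this. Planning to estimate the share of referred patients who register presupposes a count of those referred, and step 2 shows that such a count is enough for overall uptake. This stands. It does not supply the covariates of non-registrants.
2. *Only direct collection is barred.* The restriction concerns contacting decliners and collecting data from them. Clinic-held referral data are not excluded. This also stands, and it makes a remedy possible, but no such source is named.
3. *The article is condensed.* A fuller protocol might name a source for referral demographics. That is fair as far as it goes. The point, however, is that the data sources the article does describe conflict with an analysis it commits to. No fuller text could make app PROMs available for people who never registered.
4. *Uptake may mean use after registration.* The sentence sits under a heading on usage and follows one on logins. On that reading the first model has two outcome levels and valid covariates. Against it, the objectives define reach as a proportion of eligible patients, and the Equality section lists recruitment separately from usage and retention.
5. *Professionals may enter the demographics.* This is true, but the entry is still tied to first registration, so decliners and patients never offered the DHI remain absent.

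A reader might also infer that objectives 3 and 4 fail as a whole and that a digital divide would pass unnoticed. That goes too far. Use, retention, outcomes, interactions with outcome and costs do not need non-registrants, and the qualitative work in WP2 and WP4 can reveal barriers to uptake even though it cannot quantify a gap.

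**Conclusion.** The concern holds for registration only. From the data described, demographic predictors of registration are not identifiable, and baseline PROMs completed in the app cannot predict it on any reading. Overall uptake among those referred may be estimable, provided the implied referral count is in fact available. Logistic models of use and retention among registrants are sound in this respect, as are the outcome models.

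The size can be shown only by illustration. With an assumed 20% of registrants in a disadvantaged group, the uptake odds ratio could lie anywhere from 2.25 to 0.375 for an unobserved share of 10% to 40% among non-registrants. These shares are not trial data. The conclusion assumes that uptake and recruitment mean registration with the DHI, as the objectives and the Equality section indicate, and that no other source of referral demographics exists beyond what the article describes.

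**What to change.** 1. Remove baseline clinical factors from any model of registration. Keep them for use and retention among registrants.
2. Obtain indirectly, from the clinics, anonymous aggregate counts (or pseudonymised referral records) of patients referred or offered the DHI, by age, gender, ethnicity and Index of Multiple Deprivation. Analyse registered out of offered on these factors. Grouped binomial data with an allowance for clinic is one suitable form, not the only one.
3. Where a clinic cannot supply such counts, report overall uptake only, limit individual-level logistic regression to use and retention among registrants, and state that differential uptake is not estimable there.

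The cost is one aggregate table per clinic and a few sentences of protocol text. If only aggregate counts are supplied, the predictors will be coarse. Some clinics may not supply counts, so the uptake analysis may cover only part of the network.
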